#### Tertiary outcomes: efficacy and economics

Number and proportion of teeth with decay progression/no change/arrest at tooth surface level between trial arms: The number of teeth with decay progression no change/arrest will be modelled in terms of treatment group and covariates (stratification variables), considering clustering. The mean number of teeth will be presented along with 95% confidence intervals for the difference. The number of teeth with decay progression will be expressed as a percentage and subject to a similar model based approach.Statistical Analysis of HRQoL Endpoints: The EQ-5DL will be presented by each of the 5 domains descriptively. In addition, the raw responses will be converted into utilities and the mean difference between treatments presented along with 95% CIs. In addition, the quality adjusted life year (QALY) will be constructed to provide preliminary estimates of QALYs which will also be compared between groups.Statistical Analysis of Economic Endpoints: Health resource use will be summarised by treatment group. The costs associated with health resource use will also be summarised.

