### Trial design and setting

This feasibility study will be a single centre, multi-site cluster randomised controlled assessor blind parallel group (3 groups) trial, with a nested qualitative component.

A flow diagram for the trial is provided in Fig. 1. Intervention delivery and follow up will be over 12 months and will be conducted in six London care homes housing between 60 and 80 residents. The sample will be stratified to attain balance in each arm between nursing and residential care.

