### Randomisation

Randomisation will be at the care home level. (i.e. site level).

Residents will be screened for eligibility at each site, and demographic data (age, gender, level of supportive care) will be collected. This will then be used to assess distribution of participant characteristics between the arms, and if a minimisation algorithm needs to be used. This will minimise for age (65–84 vs 85 +), gender (male vs female) and level of supportive care (nursing vs residential) where possible.

Randomisation service will be provided by The UKCRN registered Institute of Kings Clinical Trial Unit. Randomisation will be to a 1:1:1 ratio, undertaken within 7 days of the final baseline resident examination.

As the trial is an open label no emergency code break is required.

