### Follow up of participants

Participants will be followed up over 12 months (Table 1).

**Table 1 Tab1:** Trial procedures by visit

Visit	Procedures to be performed
Screening	Complete process for written informed consent with resident or legal representative (including mental capacity assessment)
	Gather demographic information
	Complete medical history
	Review concomitant medications
	Brief oral examination
	Eligibility assessment
Baseline examination (within 28 days of screening)	Changes to mental capacity
	Examination using ICDAS root caries scoring system undertaken by blinded assessor
	Review concomitant medications
	Adverse event monitoring
	Undertake in depth interviews with residents to consider acceptability, QoL (OIDP and EQ5D5L and EQ5D3L survey tool) and relative need (IoRN2)
	Compliance check
	IMP administration
	Reissue 1450 ppm fluoride toothpaste to Arm1 and Arm 3 and 2800 ppm to Arm 2
	Placement of fluoride varnish by trained hygienist to Arm 3
	Complete qualitative interviews with organisational teams
	Brushing charts to be issued
	Collect health care use data for year preceding and intervention year
	Collect resource costs data from the care home
	Completion of data collection forms for resource cost data from the care home/ dental team
Randomisation	Randomisation of homes within 7 days of last baseline visit
3 months from baseline (± 3 days)	Assess changes to mental capacity
	Review concomitant medications
	Adverse event monitoring
	Administer QoL (OIDP and EQ5D survey tools) and relative need (IoRN2)
	IMP administration
	Reissue 1450 ppm fluoride toothpaste to Arm1 and Arm 3
	Reissue 2800 ppm fluoride toothpaste to Arm 2
	Placement of fluoride varnish by trained hygienist to Arm 3
	Brushing charts to be issued
6 months from baseline (± 3 days)	Assess changes to mental capacity
	Examination using ICDAS root caries scoring system undertaken by blinded assessor
	Undertake in depth interviews with residents to consider acceptability, QoL (OIDP and EQ5D survey tools) and relative need (IoRN2)
	Compliance check
	Review concomitant medications
	Adverse event monitoring
	IMP administration
	Reissue 1450 ppm fluoride toothpaste to Arm1 and Arm 3
	Reissue 2800 ppm fluoride toothpaste to Arm 2
	Placement of fluoride varnish by trained hygienist to Arm 3
	Brushing charts to be issued
	Collect health care use data for year preceding and intervention year
	Collect resource costs data from the care home

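### The caries count models adjust only for the stratification variables, leaving out teeth at risk and baseline active lesions; home clustering is not stated for the utility and QALY comparisons

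*Protocol article*

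**What the plan says.** The analysis paragraph for the tertiary outcomes states that the number of teeth with progression, no change or arrest "will be modelled in terms of treatment group and covariates (stratification variables), considering clustering". It then says: "The number of teeth with decay progression will be expressed as a percentage and subject to a similar model based approach". No percentage analysis is described for arrest or no change.

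The stratification variables are described in two places. Under Trial design and setting: "The sample will be stratified to attain balance in each arm between nursing and residential care". Under Randomisation, a minimisation algorithm may be used if the screening data suggest a need: "This will minimise for age (65–84 vs 85 +), gender (male vs female) and level of supportive care (nursing vs residential) where possible". No dental variable appears in either list.

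For EQ-5D, "the raw responses will be converted into utilities and the mean difference between treatments presented along with 95% CIs". QALYs are described as "preliminary estimates of QALYs which will also be compared between groups". These sentences mention neither home nor baseline utility.

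The unit of allocation is clear: "Randomisation will be at the care home level". Table 1 schedules this at baseline, 6 and 12 months: "Examination using ICDAS root caries scoring system undertaken by blinded assessor". It also schedules EQ-5D at baseline and at each later visit. Homes are randomised after the last baseline examination, so these baseline values precede allocation.

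**The concern.** The efficacy outcomes are counts of teeth that changed state, or did not, after baseline. A resident with more teeth can contribute more events of every kind. A tooth can be counted as arrested only if it carried an active lesion at baseline. Both quantities come from the baseline examination, yet the parenthesis in the model sentence defines the covariates as the stratification variables alone.

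With two homes per arm, randomisation cannot be relied on to balance dentition and caries. A difference in teeth or active lesions would then appear in the count contrast as if it were an effect of the toothpaste or varnish. These estimates are preliminary, but producing them is a stated tertiary objective. Feasibility criterion 3 also rests on the variability observed in this trial.

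The utility and QALY sentences raise a related but weaker question. The compliance and caries analyses both say that clustering will be considered. The utility intervals do not, although the same six homes were the units allocated.

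**Working it through.** **Inputs from the sample size section.** Two homes per group, 30 residents per home on average (60 per group), ICC of at least 0.01, SD 0.65 for change from baseline, difference 0.4, two-sided 5%. The ICC of 0.05 used below is an assumption.

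**1. The article's own figure.** Design effect DE = 1 + (30 − 1) × 0.01 = 1.29. SE = 0.65 × √(2 × 1.29/60) = 0.135. Power = Φ(0.4/0.135 − 1.96) = 84.3%, against the stated 84%. Without the design effect it would be 92.1%, so the sample size does allow for clustering.

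**2. Chance difference between two arms in a baseline variable, in SD units.** √(2 × DE/60):

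| Design | DE | SD of the difference |
|---|---|---|
| Individual randomisation | 1 | 0.18 |
| Homes, ICC 0.01 | 1.29 | 0.21 |
| Homes, ICC 0.05 (assumed) | 2.45 | 0.29 |

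**3. How this enters the counts.**
- Let the risk per tooth be p in both arms, so that there is no treatment effect. The expected progression count is p × teeth. At equal p, a resident with 14 teeth (the survey average for dentate over-85s given in the Background) has 14/5 = 2.8 times the expected count of a resident with 5, the eligibility minimum.
- If mean teeth differ between arms by d, mean counts differ by p × d. Dividing by teeth at risk removes this. The article does so only for progression.
- For arrest, the expected count is q × a, where a is the number of teeth with an active lesion at baseline and q is the chance of arrest per such tooth. Dividing by all teeth would leave differences in a in place; the denominator has to be a.
- In SD units, a typical shift in the count contrast is r × 0.21 outcome SDs at ICC 0.01, where r is the correlation between the baseline quantity and the count. The article gives no r. For assumed values of 0.3, 0.5 and 0.7 the shift is 0.06, 0.10 and 0.15 SD.

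**4. Utility and QALY intervals, if home were ignored.** True coverage of a nominal 95% interval = 1 − 2 × [1 − Φ(1.96/√DE)].
- ICC 0.01, 30 per home: 1.96/1.136 = 1.726, coverage 91.6% (error 8.4%).
- ICC 0.05 (assumed), 30 per home: 1.96/1.565 = 1.252, coverage 79.0% (error 21.0%).
- At 19.5 per home (30 less 35% attrition), the error rates are about 7% and 16%.

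These figures use normal quantiles. Six homes in three arms leave about 6 − 3 = 3 between-home degrees of freedom, with t = 3.18. A valid interval at ICC 0.01 is then about 1.136 × 3.18/1.96 = 1.84 times the naive width.

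**The case against.** **Clustering is already handled for caries.** This stands. The model sentence includes clustering, the percentage analysis follows a similar approach, and the stated power is reproduced only with the design effect. A reader might infer that home effects pass unmodelled into the caries results; the text does not support that. Unmodelled clustering would in any case make intervals too narrow rather than bias the estimates.

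**The outcomes already use baseline.** This stands in part. Progression, arrest and no change are transitions from the baseline examination, and the percentage analysis deals with number of teeth for progression. A transition count still depends on how many teeth could make the transition. The title of the analysis item can be read as promising proportions for all three states, but the outcome list and the analysis text give one only for progression.

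**Covariate detail belongs in the statistical analysis plan.** For utilities and QALYs this largely stands: the article is silent and does not state an unadjusted analysis. It is weaker for caries, where the article names the covariate set.

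**A gain in power cannot be claimed.** This stands. It would need an assumed correlation, the SD of 0.65 is already for a change from baseline, and normal-quantile power would not be reached with about 3 between-home degrees of freedom.

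**These are tertiary outcomes of a feasibility trial.** True, and it limits the consequence. No feasibility criterion depends on a between-arm caries or utility contrast.

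**Conclusion.** The point holds for the caries models. The stated covariates omit teeth at risk and baseline active lesions, on which the counts depend by construction, and only progression has a percentage analysis. The chance imbalance to expect is about 0.21 SD at ICC 0.01 with 30 residents per home, and 0.29 SD at an assumed 0.05. How far it moves the count differences depends on a correlation the article does not give. This is a shift in the result for the allocation actually drawn; it does not make a properly clustered interval invalid.

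The utility and QALY point is secondary. Clustering is stated for caries and not there. The coverage of 91.6% applies only if home is in fact ignored, at ICC 0.01 with 30 per home and normal quantiles. It would be wrong to conclude from the article that these analyses will be unadjusted. The brushing comparison is described only as model based, and no error is shown there.

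**What to change.** - **Progression and no change:** add resident-level baseline caries to the models, and include teeth or surfaces at risk at baseline as an offset or denominator. Name the unit, tooth or surface, and keep it the same throughout.
- **Arrest:** use baseline active lesions as the denominator, in the same unit as the outcome, and say how residents with none are treated.
- **Utilities and QALYs:** state the same home-level clustering as for caries, with small-sample degrees of freedom, and adjust for baseline EQ-5D utility.
- Enter the added covariates at resident level, since six homes support very few home-level terms.

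The cost is a few sentences in the analysis section or the statistical analysis plan, fixed before outcome data are analysed. The caries and utility values come from the baseline examination and EQ-5D assessment already in Table 1, so no new data collection is needed.

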### Trial data governance

#### Trial management group

A trial management group will convene 3 monthly to monitor trial progress and review any adverse events.

The group will consist of the lead researcher, representative of the CTU, Consultants in Dental Public Health. As deemed appropriate, by the research team a representative from the care homes will also be invited to attend.

### Access to source data and documents

The Investigator(s) will permit trial-related monitoring, audits, REC review, and regulatory inspections by providing the Sponsor(s), Regulators and REC direct access to source data and other documents (e.g. patients’ case sheets, blood test reports, X-ray reports, histology reports etc.).

### Ethics & regulatory approvals

The trial will be conducted in compliance with the principles of the Declaration of Helsinki (1996), the principles of GCP and in accordance with all applicable regulatory requirements including but not limited to the Research Governance Framework and the Medicines for Human Use (Clinical Trial) Regulations 2004, as amended in 2006 and any subsequent amendments.

This protocol and related documents will be submitted for review to The Social Care Research Ethics Committee (SREC), and to the Medicines and Healthcare products Regulatory Agency (MHRA) for Clinical Trial Authorisation

The Chief Investigator will submit a final report at conclusion of the trial to the KHP-CTO (on behalf of the Sponsor), the REC and the MHRA within the timelines defined in the Regulations

### Quality assurance

Monitoring of this trial will be to ensure compliance with Good Clinical Practice and scientific integrity will be managed and oversight retained, by the KHP-CTO Quality Team.

In considering risk relating to the investigational medicinal product (Duraphat® 2800 ppm and varnish) risks to participants would be no higher than that of standard medical care (classified a type A based on MRC/DH/MHRA Joint Project 2011). The licensed medicinal products being used will be used for their licensed range of indications, dosage and form in this study, and so this has been determined as a low-risk trial.

### Data handling

The Chief Investigator will act as custodian for the trial data. The following guidelines will be strictly adhered to:Patient data will be pseudo- anonymised*.*All pseudo-anonymised data will be stored on a password protected computer.All trial data will be stored in line with the Medicines for Human Use (Clinical Trials) Amended Regulations 2006 and the Data Protection Act and archived in line with the Medicines for Human Use (Clinical Trials) Amended Regulations 2006 as defined in the Kings Health Partners Clinical Trials Office Archiving SOP.

### Data management

An electronic CRF will be used provided by King’s College London Clinical Trials Unit. A separate data management plan will be created for the trial.

Confidentiality: The participants will be identified in the database only by initials and a participant study identification number. The study will comply with the Data Protection Act Names and any other identifying detail will NOT be included in any study data electronic file. Anonymised data documents will be stored in a locked cupboard at the sponsor site.

### Insurance/indemnity

King’s College London holds insurance against claims from participants for harm caused by their participation in this clinical study. Participants may be able to claim compensation if they can prove that KCL has been negligent.

### Dissemination

Research in care homes is limited, and in addition very few clinical trials have been conducted in this setting with vulnerable groups. The findings from this study will hold value not only academically, but also to key stakeholder groups including residents, families, care staff, care home and patient representative organisations, dental healthcare providers and commissioners locally and nationally as well as regulators of social care and broader public health landscape.

The working group have developed a dissemination strategy as the trial progresses. The outputs will be based on three broad areas, academic, stakeholder and policy.

The principal outputs for the project will be peer review publications, posters and presentations at regional, national and international conferences, such as European Association for Dental Public Health and International Association for Dental Research.

We will present at meetings and local events with stakeholders, including NHS and Local Authority colleagues to raise the importance of the agenda. We will also send a summary report through a newsletter to all stakeholders involved in the programme, including each care home that has taken part.

It is important that this work is presented at a broader level with a view to inform policy. We will therefore actively seek opportunities to present and publish the work at Public Health England, Chief Dental Officer and NHS meetings and conferences and meetings.

## Discussion

This trial will produce new knowledge and add value to a landscape that is under researched.

Although the efficacy of fluoride interventions is proven, the feasibility of dental research and prevention in this vulnerable group and in the complex care home setting is novel. This work will not only add to our understanding of the interface of dental care and social care but will also contribute to our broader understanding on undertaking research in care home settings. In addition, although the work is set in care homes, there is also applicability of this research to those living in their own homes.

One of the challenges already highlighted in setting up the study is the lack of a coherent structured clear process for setting such trials up. Care home residents not being deemed NHS patients if the research is delivered in their ‘home’ sets up a unnecessary barrier to research in this setting. Equally challenging, is the necessary ethical approval process, that seeks to protect the participant, but can also hinder the value of including all participants in research.

Delivering interventions for vulnerable care home residents, with complex medical and behavioural challenges and high levels of both personal and dental care needs, although clinically beneficial, may not be feasible. The complexities of ethics, consent, capacity and acceptability need to be carefully thought out as to ensure benefit to the residents in their ‘real life’ environment, so that public health programme development is based not only in the science but in the application.

Dental care for older people has been a longstanding issue, and the events of this past year has shone a light on the vulnerabilities of those residing in care homes. In addition, there is a focus on preventative public health and with the fact that dental health and general health are intrinsically linked, this research is landing at a pivotal time.

### Protocol versions

V1.0 Original 26th October 2017.

V2.0 1st January 2019 (change of named statistician).

### Trial status

The trial was paused due to Covid-19 and data collection points were delayed. We are now discussing re-entering care settings to continue the trial. The study team need to consider recruitment plans and timelines in light of the current status in care homes and the number of losses in the last year due to the pandemic.

## Data Availability

Not applicable.

## Abbreviation

ICDAS: International caries detection and assessment system
